#### **8.12.1     Statistical Analysis**

All data will be background subtracted and compared using **two-sided t-tests** as described above.

## **9 SAFETY MONITORING**

### **9.1 Potential Benefits**

Based on experience with immunization in our previous vaccine trials, immunotherapy may be of benefit to subjects with MGs. Of course, because individuals respond differently to therapy, no one can know in advance if it will be beneficial in an individual case. The potential benefits may include reduction and/or remission of the subject's brain cancer. Because this procedure is experimental, it cannot be guaranteed that subjects will receive any benefit as a result of participating in this research study. The information collected in this research may help scientists better understand the mechanisms involved in the immune system's ability to fight cancer. If such an understanding comes from this research, then it may benefit society by furthering the development of improved treatment methods for human malignant brain tumors in the future.

### **9.2 Potential Risks**

#### **9.2.1 Allergic Reactions to EGFRvIII Vaccination**

Injection of PEPvIII peptide or KLH may result in an allergic reaction, which could include redness and swelling at the injection site, itching, hives, low blood pressure, difficulty breathing, or in the most extreme circumstances, death. In addition, if the immune system becomes overly activated, potential discomforts may include pain, redness and swelling at the injection site.

#### **9.2.2 GM-CSF**

Injection of GM-CSF may increase the risk of infection, lower platelets, or cause fluid retention. GM-CSF also may result in an allergic reaction, which could include redness and swelling at the injection site, itching, hives, flushing, syncope, low blood pressure, difficulty breathing, or in the most extreme circumstances, death. In addition, if the immune system becomes overly activated, potential discomforts may include pain, redness and swelling at the injection site.

#### **9.2.3 Cerebral Edema**

Cerebral edema may be secondary to the disease process itself, the surgical procedure, necrosis from previous radiation, or inflammation due to immune infiltration of the brain or destruction of tumor cells. Symptoms may include, but are not limited to, severe headache, confusion, lethargy, unresponsiveness, coma, or focal neurological deficits. Patients will be monitored throughout the course of the study and those patients with any signs or symptoms of cerebral edema may need their steroid doses increased, treatment with an osmotic diuretic, or surgical decompression. Edema that fails to respond to aggressive therapy may lead to permanent neurological impairment. The probability of this risk can be predicted to some degree based upon tumor size, location,

pre-operative neurological impairment, and post-operative course prior to vaccinations. Patients will be monitored throughout the course of the study.

#### **9.2.4      Infection**

The CDX-110 vaccine may include the risk of infection due to potential contamination of the leukocyte product in the laboratory. This may result in localized redness, swelling, or induration at the injection site. In the most extreme situation, this may lead to systemic bacterial/fungal sepsis and possibly death. The probability of this risk is relatively low, given the small injection volume (1 mL divided between >2 intradermal locations) and the fact that the CDX-110 will be strictly tested for sterility prior to each injection. The risk of infection due to potential contamination of the CDX-110 in the laboratory will be minimized by biosafety quality assurance and testing. All cell cultures will be handled under sterile conditions in a core tissue culture facility dedicated to the processing of human cells. Prior to injection into patients, vaccines must pass sterility tests in thiglycolate broth, tryptic soy blood agar, and inhibitory Sabouraud agar. Following injections, patients will be monitored throughout the course of the study for any signs and symptoms of infection. There have been no infections to date in the recent VICTORI (IRB #3108-05-9R4) or ACTIVATE (IRB #5421-05-1R1) clinical trials testing similar approaches in a similar patient population. If an active infection is suspected, patients will be cultured and treated with appropriate antibiotics.

#### **9.2.5      Delayed Autoimmune Diseases**

It is possible that delayed autoimmune disease(s) may develop as a result of injection with CDX-110. This means that the immune system may be stimulated to attack natural tissue in the body. Animal studies have reported the development of autoimmunity in the context of vaccination and recovery from lymphopenia. However, our current experience with CDX-110 vaccination in glioma patients has not demonstrated evidence of autoimmunity in treated patients. Furthermore, the doses of TMZ used in this study for induction of lymphopenia are standard doses administered to patients with GBM. It therefore, is unknown what the risk of delayed autoimmune disease is for this study.

#### **9.2.6      Phlebotomy**

Drawing blood or inserting an intravenous catheter into an arm vein may result in bruising or swelling in the area of the insertion, bleeding at the site of the needle puncture, light headedness, fainting and very rarely, local infection, which may be severe. These risks are reduced by the fact that the blood will be drawn by a qualified physician, nurse or phlebotomist (a professional trained to draw blood).

#### **9.2.7      Leukapheresis**

As with any donation of blood, a variety of minor reactions may occur with leukapheresis, which include fainting, dizziness, or nausea. Uncommon but serious complications may also result, which include bleeding, infection, an adverse reaction to

the anticoagulant or replacement fluids, hypocalcemia, hypotension, shock, convulsions, air emboli, heart failure, or the inability to transfuse blood back into the patient. These risks are reduced by the fact that the procedure will be performed by qualified staff at a specialized clinical hemapheresis unit. Patients will be carefully monitored throughout the procedure by trained nursing and medical staff. Calcium gluconate (2 mg PO) will be given to minimize the risks of hypocalcemia, fluid supplementation will be given to minimize hypotension, and blood will be routinely screened for *HIV*, hepatitis, and syphilis to minimize the risk of transmitting infection.

### **9.2.8      MRI**

The risks and/or discomforts associated with the performance of MRI include the anxiety produced from being in a tight, enclosed space (claustrophobia). In addition, the machine operates using a large and powerful magnet. The magnetism of the machine attracts certain metals: therefore, people with these metals in their bodies (specifically pacemakers, infusion pumps, metal aneurysm clips, metal prostheses, joints, rods or plates) will be excluded from the study. Patients will also be checked to make sure that they do not bring any metal objects into the MRI facility. Dental fillings are less affected by the magnetic fields generated and are therefore permitted. It will be asked that patients let the physicians conducting this study know of any metal in their bodies other than dental fillings.

### **9.2.9      Allergic Reactions to Contrast Agents**

During the MRI, patients will be given a contrast agent. The agent is given routinely to obtain enhanced MRI scans of the brain. The agent is administered through the vein and requires the placement of an IV catheter. The catheter placement is similar to drawing blood except that the catheter remains in the vein during the time the agent is actively delivered. The risks of a blood draw and insertion of a catheter are similar. There have been a few, rare cases of allergies to the agent used in MRI contrast enhanced scans. Patients with any known severe allergies to contrast agents will be excluded from the study. Patients with mild allergies (i.e., rash only) will be pretreated with Tylenol and Benadryl prior to injection of the contrast agent.

### **9.2.10     Temozolomide**

TMZ has been well tolerated by both adults and children with the most common toxicity being mild myelosuppression. Other, less likely, potential toxicities include nausea and vomiting, constipation, headache, alopecia, rash, burning sensation of skin, esophagitis, pain, diarrhea, lethargy, hepatotoxicity, anorexia, fatigue and hyperglycemia. Hypersensitivity reactions have not yet been noted with TMZ. As in the case with many anti-cancer drugs, TMZ may be carcinogenic. Rats given TMZ have developed breast cancer. The significance of this finding for human is not presently known. TMZ therapy will be followed but given as standard of care. If toxicities occur, the Principle investigator and primary physician will titrate therapy based on standard clinical guidelines as outlined above.

### **9.2.11 Daclizumab**

In trials of renal transplantation, the overall incidence of infectious episodes, including viral infections, fungal infections, bacteremia and septicemia, and pneumonia was not higher in the daclizumab-treated patients than the placebo-treated patients. There was, however, a slight increase in wound infections, specifically, with daclizumab. Addition of daclizumab also did not increase the number of post-transplant lymphomas up to three years post-transplant. No difference in abnormal hematologic or chemical laboratory test results were seen between groups treated with placebo or daclizumab with the exception of fasting blood glucose which was likely related to corticosteroids or diabetes. While low titers of anti-idiotypic antibodies to daclizumab were detected in adult patients treated with the drug, no antibodies that affected efficacy, safety, serum daclizumab levels or any other clinically relevant parameter examined were detected.

### **9.2.12 Unknown Risks**

The overall risk classification of this research is unknown. Clinical trials using CDX-110-based immunizations on brain tumor patients only recently published in the literature. From our experience with 40 patients in ongoing and previous trials we have not seen any toxicities or serious unexpected adverse events.

### **9.2.13 Confidentiality**

Participation in research investigations may result in a loss of confidentiality. However, all data from preoperative and postoperative evaluations will be coded to protect the patient's identity. The coding, and the results of these studies will be available only to the individuals involved with the study, the clinical staff administering the study, representatives of the National Institutes of Health, and representatives of the U.S. Food and Drug Administration. Any publications resulting from this study will not use patient identifying data.

### **9.2.14 Treatment Alternatives & Financial Reimbursement**

Alternative treatments for recurrent malignant brain tumors include additional surgery, radiation, and/or chemotherapy. If the patient chooses not to participate in this trial, they certainly may seek alternative treatment. If the patient fails treatment through this trial, these alternatives may still be available to the patient. There will be no financial reimbursement to subjects for study participation.

## **9.3 Data and Safety Monitoring Plan**

This clinical research study will be monitored both internally by the PI and externally by the Duke University Medical Center Cancer Center's Protocol Review and Monitoring system in accord with their NCI-approved "Institutional Protocol Monitoring Procedures and Guidelines for NIH-sponsored Research Involving Human Subjects." In terms of internal review the PI will continuously monitor and tabulate adverse events. Appropriate reporting to the Duke University Medical Center IRB will be made. If an

unexpected frequency of grade III or IV events occur, depending on their nature, action appropriate to the nature and frequency of these adverse events will be taken. This may require a protocol amendment, dose de-escalation, or potentially closure of the study. The PI of this study will also continuously monitor the conduct, data, and safety of this study to ensure that:

- Interim analyses occur as scheduled;
- Stopping rules for toxicity and/or response are met;
- Risk/benefit ratio is not altered to the detriment of the subjects;
- Appropriate internal monitoring of adverse events and outcomes is done;
- Over-accrual does not occur;
- Under-accrual is addressed with appropriate amendments or actions;
- Data are being appropriately collected in a reasonably timely manner.

External review of this protocol begins with an initial review by the CPC, which performs a risk assessment of the trial. The PI will abide by their assessment of the level of risk, which will determine the intensity of subsequent external monitoring. Documentation of this assessment will be maintained. A formal, independent audit will be conducted by the Scientific Monitoring Subcommittee of the CPC after the first 3 subjects are enrolled. Assuming a “satisfactory” review, thereafter, the Scientific Monitoring Subcommittee of the CPC will review selected patients enrolled on this protocol on a bi-annual basis. This includes review of aggregate toxicity as reported in the progress report, accrual, amendments, and outcomes. If there appears to be an unexpected frequency of serious and/or unexpected toxicity or other significant issues, a full re-audit will be initiated. Any rating less than satisfactory will also prompt a full re-audit and corrective plan.

## **10 STATISTICAL CONSIDERATIONS**

### **10.1 Recruitment**

The following table lists the gender and minority breakdown for all brain tumor patients seen at Duke relative to the national incidence figures:

## PERCENTAGE

|                     | DUMC (1992-1996) n=793 |        |         | NATIONAL |        |        |
|---------------------|------------------------|--------|---------|----------|--------|--------|
|                     | MALE                   | FEMALE | TOTAL   | MALE     | FEMALE | TOTAL  |
| WHITE               | 55.5%                  | 32.3%  | 87.7%   | 48.2%    | 34.4%  | 82.6%  |
| AFRICAN
AMERICAN | 5.7%                   | 4.0%   | 9.7%    | 3.6%     | 3.6%   | 7.2%   |
| NATIVE
AMERICAN  | 0.3%                   | 0.3%   | 0.5%    | 0.1%     | 0.1%   | 0.2%   |
| ASIAN               | 0.4%                   | 0.3%   | 0.6%    | 0.7%     | 1.0%   | 1.7%   |
| HISPANIC            | 0.9%                   | 0.5%   | 1.4%    | 1.8%     | 0.8%   | 2.6%   |
| OTHER               | 0.0%                   | 0.0%   | 0.0%    | 3.3%     | 2.4%   | 5.7%   |
| TOTAL               | 62.7%                  | 37.3%  | 100.0 % | 57.7%    | 42.3%  | 100.0% |

Since the Duke Brain Tumor Program began in 1996 we have treated patients from 35 States and 11 foreign countries. The national incidence figures are the most accurate with which to compare our accruals. Our brain tumor studies are open to patients of all ages, both sexes, and all minorities. The only exclusions are the occasional incidences in which the FDA or our IRB requires that children below the age of 18 be excluded from some of our initial Phase I studies because of the potential for greater toxicity to the developing nervous system. In addition, certain diseases that we treat occur preferentially in one gender or minority than another. For example, carcinoma of the breast is a frequent cause of metastatic brain tumors and, of course, is much more common in women than in men. Although the lung cancer incidence is rising in women, the incidence is still higher in men and it is also a frequent cause of metastatic brain tumors. Primary brain tumors and metastatic brain tumors from some very common tumors such as melanoma are an infrequent disease in African-American populations. Our accrual statistics reflect the lower incidence in the African-American population. Although our accrual historically has been weighted in favor of white males, we have previously demonstrated that this bias was not present when the demographics of the patient population that was offered participation was considered, but rather only in that population that consented to participate. We will continue to actively recruit women and minorities into this study using methods that have shown previous success in recruiting the participation of these subgroups.

We routinely send letters to our primary referring physicians notifying them of our interest in including minorities and women in all our brain tumor clinical trials. The overall Duke figures for minority patients with brain tumors exceed, in most instances, the national incidence figures.

In order to ensure representative accrual to our studies, the table below has been created. It outlines estimated accrual and anticipated ethnic and sex composition for the proposed studies. Actual accrual will be reviewed after each segment and compared with

 IRB, institutional review board

this table. If the expected accrual diversity is not met, we will initiate a targeted recruitment program through techniques already established within the Duke University Medical Center including the placement of advertisements in newspapers or on radio stations catering to the underrepresented population(s) and providing educational seminars for patients and staff at community institutions such as churches and medical clinics that preferentially serve the underrepresented population(s).

Twenty patients will be accrued to this study. All patients enrolled on the study, even if taken off study prior to treatment, will be included in the data analysis for this section and those outlined below. Based on our proven accrual rate of >1 EGFRvIII+ patients per month in our completed studies and the absence of any other competing studies within the Brain Tumor Center at Duke, accrual to this study is estimated to take ~20 months to complete. It is estimated that an additional 6 months will be needed to analyze immunologic data and another 12 months to complete patient follow-up for clinical endpoints. The target distribution for patient enrollment is shown in the following Table:

| Number of Patients:                       |                    | 20            |                     |
|--------------------------------------------------|--------------------|----------------------|---------------------|
| Race                               | Male | Female | TOTAL |
| American Indian/Alaska Native             | 0                  | 0                    |                     |
| Asian                                     | 0                  | 0                    |                     |
| Native Hawaiian or Other Pacific Islander | 0                  | 0                    |                     |
| Black or African-American                 | 1                  | 1                    |                     |
| White                                     | 10                 | 8                    |                     |
| TOTAL                                     | 11                 | 9                    | 20                  |
| Ethnicity                          |                    |                      |                     |
| Hispanic or Latino                        | 0                  | 0                    |                     |
| Not Hispanic or Latino                    | 11                 | 9                    | 20                  |

A second cohort of 6 patients (cohort #2) will receive serial administrations of daclizumab at vaccines # 1 and 3 and during the recovery from first 3 TMZ cycles at the same dose. Patients with progressive disease during radiation, dependent on steroid supplements above physiologic levels at time of vaccination, and are unable to tolerate TMZ will be replaced. As a result, 12 patients will be consented but a maximum of 6 patients will receive 3 vaccines and 5 cycles of daclizumab. In cohort #2, patients who do not complete 4 vaccines and 2 doses of daclizumab will be replaced. Based on a predicted accrual rate of 2 patients each month, it is estimated to take 3-6 months to complete this additional cohort. The target distribution for patient enrollment is shown in the following Table:

|           | Patient Numbers | White |        | African-American |        | Hispanic |        | Asian |        | Other |        |
|-----------|-----------------|-------|--------|------------------|--------|----------|--------|-------|--------|-------|--------|
|           |                 | Male  | Female | Male             | Female | Male     | Female | Male  | Female | Male  | Female |
| Cohort #1 | 20              | 10    | 7      | 1                | 1      | 0        | 0      | 0     | 0      | 1     | 0      |
| Cohort #2 | 6               | 3     | 2      | 1                | 0      | 0        | 0      | 0     | 0      | 0     | 0      |
| TOTAL     | 26              | 13    | 9      | 2                | 1      | 0        | 0      | 0     | 0      | 1     | 0      |

## **10.2 Safety Component**

The study statistician, [name], Ph.D., will be responsible for all statistical analysis. Establishing the safety and efficacy of intradermal immunization with CDX-110 with or without daclizumab will be an important goal of this study and the methods for determining this are outlined above.

Given the lack of significant toxicity in our prior multi-institutional EGFRvIII-targeted immunotherapy trials and those of others in patients with GBM(Yu, Wheeler et al. 2001), and the established safety of the clinically-approved drug daclizumab, and the safety of other clinical approaches to TReg inhibition that have been used recently(Dannull, Su et al. 2005), we believe that it is likely that no significant toxicity will occur. However, any irreversible Grade 3 or reversible Grade 4 toxicity or life-threatening event, prior to tumor progression, will be considered a limiting toxicity. Patients will be randomized to each group in blocks of 3 and patients will be evaluated for toxicity within these groupings. If no patients in a given cohort experience a toxicity within 2 weeks another cohort will be enrolled within that arm. Enrollment will be halted if:

1. Any two patients in a cohort of three experience a DLT; or,
2. Any two patients in a cohort of six consecutively enrolled patients experience a DLT.

Because we have previously safely treated many patients with the vaccine alone, toxicity in each arm will be evaluated independently. We have an existing Data and Safety Monitoring Plan approved by the NCI (See Appendices) for use in these studies.

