### **5.2 Treatment Procedures**

#### **5.2.1 Vaccination**

After initial leukapheresis, all patients will then receive RT and concurrent TMZ at a standard targeted dose of 75 mg/m^2/d. Patients with progressive disease during radiation, dependent on steroid supplements above physiologic levels at time of vaccination, unable to tolerate TMZ or whose PBLs fail to meet release criteria will be replaced, but no more than 40 patients will be enrolled overall. Remaining patients will then receive the initial cycle of TMZ at a targeted dose of 100mg/m^2/d for 21 days 3 ± 1 weeks after completing RT and will be independently randomized to receive daclizumab versus saline simultaneous with vaccine #1. An additional cohort of 6 patients (cohort #2) will receive serial administrations of daclizumab during vaccine # 1, vaccine # 3, and during the recovery from each TMZ cycle for first 3 cycles at the same dose. Vaccine #1 will be given on day 21 ± 2 days after the start of the 100mg/m^2/d dose of TMZ. Each immunization will be divided equally to both inguinal regions. A total volume of 200 µL

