## 8 IMMUNOLOGIC MONITORING AND STATISTICAL ANALYSIS

Immunological response evaluations for baseline values will be conducted on the pre-vaccine leukapheresis sample. An additional leukapheresis will be required for any patients who have a positive DTH skin test for PEPvIII for immunologic monitoring. Immunologic response evaluations will also be performed from peripheral blood obtained. A comparison of pre-therapy lymphocyte functions to those at intervals after each immunization and subsequently will be made. These tests may provide evidence for the inhibition of  $T_{Reg}$  function or a change in the quantity or quality of immune responses following CDX-110 immunization and will play an important role in the design of future CDX-110-based clinical trials.

Clinical and immunologic endpoints will be analyzed in all patients and statistical considerations described below are powered based on enrollment of 20 patients. However, an analysis of patients stratified at enrollment based on complete resection or residual disease will be performed for hypothesis generation on the role of tumor burden on clinical and immunologic responses to PEPvIII vaccination and daclizumab.

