### **8.1.1 Overview of Statistical Analysis**

Our laboratory and the HVTN Immunologic Monitoring Reference Laboratory, headed by [name] also at Duke University, has devoted considerable effort to co-developing and co-validating the immunologic assays outlined below for monitoring  $T_{Reg}$  function, antigen-specific responses in CD8+ or CD4+ T-cells, and NK cell functional activity in cancer patients. The reproducibility of these assays in our hands ensures that they can be reliably used for monitoring of changes after vaccination with and without daclizumab. Power calculations for this study are based on our primary endpoint which is functional suppressive capacity of CD4+CD25+CD127-  $T_{Regs}$ . For these calculations, we assumed that measurements made in each treatment group at a given phytohemagglutinin (PHA) level would be normally distributed with standard deviation of  $\sigma$ . Based on our experience with these assays within this patient population (Fecci, Mitchell et al. 2006), we estimate that with a sample size of 20 randomized patients we will have 80% power to detect a difference of 1.41  $\sigma$  at the 0.017 significance level (one-tailed). A 0.017 level of significance is used to adjust (Bonferroni correction) for the use of 3 non-zero PHA doses (0.1, 1, 10  $\mu$ g/well) in the proliferation assay. Thus, with only 20 patients, we will have sufficient power to detect treatment effects much more subtle than the ones observed in our pre-clinical studies (Fecci, Sweeney et al. 2006) and effects that we believe would be clinically significant. However, because the magnitude and variability of the effects of daclizumab on  $T_{Regs}$  remain unknown in humans, once human data become available from these studies, power analyses will be recalculated and patient numbers adjusted if needed. If daclizumab treatment does not significantly inhibit the functional recovery of  $T_{Regs}$  (primary endpoint), we would not be interested in the further development of this drug as

a vaccine adjuvant. Therefore, a one-sided hypothesis test is utilized. Power calculations are not provided for subsequent analyses as the number of patients in this trial will be determined by the primary endpoint, and the remainder of the analyses is exploratory and hypothesis generating only. With 10 patients in each arm, however, we will have 80% power to detect difference  $>1.325\sigma$  between groups for each assay at  $\alpha=0.05$ .

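### Randomising two arms in blocks of 3, tied to the toxicity cohorts and with no ratio stated, does not assure the 10:10 split behind the power figures and may make places in a block predictable

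*Protocol*

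**What the plan says.** The allocation rule stands in the Protocol, 10.2 Safety Component: "Patients will be randomized to each group in blocks of 3 and patients will be evaluated for toxicity within these groupings". The sentence after it makes the same groups of three serve as safety cohorts: "If no patients in a given cohort experience a toxicity within 2 weeks another cohort will be enrolled within that arm". The section names no ratio within a block, no pattern across blocks and no rule for an incomplete last block.

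Other sections assume something different:

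- Section 5.2.1 says that patients remaining after radiotherapy "will be independently randomized to receive daclizumab versus saline simultaneous with vaccine #1". The synopsis and 5.1.1 say the same. This describes two arms and allocation patient by patient.
- Section 8.1.1 bases the primary endpoint on this statement: "with a sample size of 20 randomized patients we will have 80% power to detect a difference of 1.41". The figure is in units of sigma, and the test is one-sided with alpha 0.017. For the other assays the section states the split outright: "With 10 patients in each arm, however, we will have 80% power to detect difference". There the difference is 1.325 sigma and alpha is 0.05.
- Section 10.3 builds its 6-month survival test (35% against 75%, alpha = beta = 0.1) on 10 patients per arm.
- Sections 4.2.4 and 4.2.6 allow an enrolled patient to be removed and replaced for steroid need at the first vaccination or for temozolomide intolerance.

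**The concern.** A block exists to hold the arms at the planned ratio, and a block of 3 cannot do this for two arms at 1:1. Neither 10 nor 20 is a multiple of 3, so the target is not a whole number of blocks either.

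The source of the trouble appears to be that a toxicity cohort of three has been used as the randomisation block. Read with the phrase about enrolling another cohort in the same arm, 10.2 could mean that whole threes go to one arm. The wording in 5.2.1 could not mean that. A person preparing the list cannot tell which is intended, and the choices lead to different trials.

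Two things are at stake. The first is the split that the stated operating characteristics depend on. The second is concealment: the smaller and more regular the block, the more a known history reveals about the next assignment, and this trial has a decision to keep or replace a patient close to that moment. Section 8.3.1 relies on random assignment when it attributes differences between the groups after vaccination to daclizumab.

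**Working it through.** **Inputs.** Two arms (5.2.1); 20 randomised patients, 1.41 sigma, one-sided 0.017 (8.1.1); 1.325 sigma at 0.05 with 10 per arm (8.1.1); 10 per arm, 35% against 75%, alpha = beta = 0.1 (10.3); blocks of 3 (10.2). Assumption: with 20 patients there are six full blocks (18 patients) and the first two places of a seventh.

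**Step 1. Reproduce the stated power.** For a two-sample t-test with 18 degrees of freedom, the noncentrality is d × √(n1·n2/(n1+n2)). At 10:10 and d = 1.41 this is 1.41 × √5 = 3.153. The one-sided 0.017 critical value is 2.295, and power is 79.7%. For d = 1.325, two-sided 0.05, power is 80.0%. Both stated figures reproduce, and both are 10:10 figures.

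**Step 2. What split does each reading give?**

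- *Whole blocks to one arm.* An arm's count is 3k, or 3k + 2 if it takes the last pair. Ten is neither, so 10:10 is impossible; the closest is 11:9.
- *Fixed 2:1.* After 18 patients the split is 12:6. The two remaining places add 1 and 1 (probability 2/3) or 2 and 0 (1/3). The result is always 13:7 or 14:6.
- *Each block 2:1 or 1:2 at random.* After six blocks an arm holds 6 + B, with B binomial(6, ½). The last two places add 0, 1 or 2 with probabilities 1/6, 4/6, 1/6. P(10:10) = (20/64)(4/6) + (15/64)(1/6) + (15/64)(1/6) = 110/384 = 29%. The range is 6:14 to 14:6.
- *Alternating 2:1 and 1:2.* 9:9 after 18 patients, then one each with probability 2/3. So 10:10 in 67%, otherwise 11:9.
- *Three per arm, in effect blocks of 6.* 9:9 after 18 patients, then one each with probability 2 × (3/6)(3/5) = 60%, otherwise 11:9 or 9:11.

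**Step 3. Power at 1.41 sigma by split.**

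| Split | √(n1·n2/20) | Noncentrality | Power |
|---|---|---|---|
| 10:10 | 2.236 | 3.153 | 79.7% |
| 11:9 | 2.225 | 3.137 | 79.3% |
| 12:8 | 2.191 | 3.089 | 78.0% |
| 13:7 | 2.133 | 3.008 | 75.7% |
| 14:6 | 2.049 | 2.890 | 72.1% |

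**Step 4. The 6-month survival test.** The rule is to accept an arm with r or more survivors. Alpha = P(X ≥ r) at 35%; beta = P(X < r) at 75%.

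| Arm size | r | Alpha | Beta |
|---|---|---|---|
| 10 | 6 | 0.095 | 0.078 |
| 9 | 5 | 0.172 | 0.049 |
| 9 | 6 | 0.054 | 0.166 |
| 11 | 6 | 0.149 | 0.034 |
| 11 | 7 | 0.050 | 0.115 |

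Ten per arm meets the stated 0.1 and 0.1. With 9 or 11, no cut-off does: the lower one breaks alpha and the higher one breaks beta.

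**Step 5. Predictability, if the block rule and past assignments are known.** Whole-arm block: the first assignment reveals the other two. Fixed 2:1: at least one place is determined, and two in one third of blocks. Random 2:1 or 1:2: at most one place, and none in two thirds of blocks.

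**The case against.** The strongest reply is that 10.2 is loosely worded rather than wrong. The phrase may mean three per arm, which suits the statement that toxicity is judged in each arm independently. The split is then 10:10 or 11:9, and primary power falls by 0.4 points at most. Section 8.1.1 also allows power to be recalculated and numbers adjusted. List generation and concealment are often kept outside a protocol, so their absence here is no fault. Saline is given in the same way as daclizumab (5.1.5), which may limit what staff know of past assignments. All of this stands, and it limits the size of the point. It does not remove it, because no reading assures 10:10, and the text does not say which one applies.

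A reader might infer more, in four ways that the documents do not support:

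- *That 10:10 cannot be reached.* This holds only for whole-arm and fixed 2:1 blocks.
- *That a split of 14:6 or worse is close to an even chance.* A figure of 45% (29/64) follows if whole blocks are assigned by unrestricted coin toss with no cap per arm, but the protocol describes no such schedule, and 5.2.1 speaks against it.
- *That treatment is confounded with assay batch.* No batching plan is given, and 8.5 uses cryopreserved cells for the cytokine cytometry assay.
- *That staff can choose whom to enrol by predicted arm.* Enrolment precedes radiotherapy, and 7.3 places vaccine 3 to 4 months after it. The exposed moment is the later one, when removal and replacement under 4.2.4 and 4.2.6 are still possible.

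**Conclusion.** The point holds in a limited form. Section 10.2 fixes a block size that cannot be balanced 1:1, states no ratio, ties the blocks to toxicity cohorts, and does not agree with the individual randomisation in 5.2.1. The chance of the 10:10 split behind 8.1.1 and 10.3 ranges from zero to about two thirds, depending on the reading.

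The cost to primary power is under 2 points at 11:9 or 12:8, and about 4 to 8 points at 13:7 or 14:6. The survival test is more sensitive, since 11:9 already takes both arms outside its stated error rates; 10.3 does not treat survival as an endpoint, so this is the lesser loss. Predictability of one or two places is a conditional risk: it requires staff to know both the block rule and earlier assignments. The protocol states no masking for this comparison, so that cannot be ruled out from the text.

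The figures assume exactly 20 randomised patients, a truncated seventh block and a t-test at a single PHA dose. The change is worth making because following the text as written can give a worse allocation than the design intends.

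**What to change.** In 10.2, replace the reference to blocks of 3 with individual 1:1 randomisation of cohort #1, using concealed permuted blocks of even size. Sizes of 2 and 4 summing to 20 are one suitable choice; other even sizes that complete at 20 would also do. With the 20 places filled, this gives exactly 10:10 and restores 79.7% for 1.41 sigma, 80.0% for 1.325 sigma, and the stated survival error rates. Varying the block size matters: in a fixed and known block of 4, an average of 1.33 of 4 places is still determined.

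State separately that toxicity is counted per arm on patients as they accumulate, independently of the allocation list. Reconcile the cohort-of-three wording in 10.2 with that in 5.3.2, so that a cohort describes how events are counted and not how patients are assigned. The halting rule itself need not change for this purpose.

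The cost is a new randomisation list and matching edits in 10.2 and 5.3.2. No patients, visits or procedures are added.
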